| Target sample size                                    | 4,000                                                                                                                                                                                                                                                                                                                                                                                                                                                                                                                                                                                                                                      |
| Study period                                          | October 2013 to March 2018                                                                                                                                                                                                                                                                                                                                                                                                                                                                                                                                                                                                                 |

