| Endpoints | 
Primary endpoint
 
 
• Recurrence of symptomatic ischemic stroke ("ischemic stroke" hereafter), with symptoms lasting for at least 24 hours
 
 
Secondary endpoints
 
 
• Any stroke [ischemic stroke (IS), intracerebral hemorrhage (ICH), or subarachnoid hemorrhage (SAH)]
 
• ICH or SAH
 
• Ischemic cerebrovascular disorder [IS or transient ischemic attack (TIA)]
 
• Death from any cause
 
• Stroke [IS, ICH, SAH], myocardial infarction (MI), or vascular death
 
• All vascular events: stroke, MI, and other vascular events [e.g. aortic dissection or rupture; pulmonary embolism; heart failure, angina pectoris, or occlusive arteriosclerosis requiring hospitalization; and revascularization of coronary artery, aorta, peripheral artery, etc.]
 
                                                                                                                                                                                                                                                                                                                                                                                                                                                                                                                                                                                                                                                                                                                              |

|                                                       |                                                                                                                                                                                                                                                                                                                                                                                                                                                                                                                                                                                                                                            |

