### **3.3. Exclusion Criteria**

Patients meeting any of the following criteria will be excluded:

- 1) Patients with emboligenic heart disease (See 29. *References*)
- 2) Patients taking any anticoagulant agents
- 3) Patients who cannot undergo MRI examination for reasons such as claustrophobia or implanted pacemaker
- 4) Patients scheduled to undergo any surgery during the study period, including percutaneous angioplasty, stent placement, or bypass grafting
- 5) Patients with a drug-eluting coronary stent implanted within the past year
- 6) Patients with a history of symptomatic non-traumatic intracranial hemorrhage, any other hemorrhagic disease (e.g. active peptic ulcer), bleeding predisposition, or blood clotting disorders
- 7) Patients with a history of hypersensitivity to cilostazol
- 8) Patients with congestive heart failure or uncontrolled angina pectoris
- 9) Patients with thrombocytopenia (platelet count  $\leq 100,000/\text{mm}^3$ )
- 10) Patients with severe liver or renal dysfunction (See 29. *References*)
- 11) Women who are pregnant, breast-feeding, or of child-bearing potential
- 12) Patients with malignant tumor requiring treatment
- 13) Patients who are taking aspirin and meet any of the following criteria:
  - History of hypersensitivity to aspirin or salicylic acid analogues
  - Peptic ulcer complication
  - Aspirin-induced asthma or its history

- 14) Patients who are taking clopidogrel, and meet the following criterion:
  - History of hypersensitivity to clopidogrel
- 15) Patients who are participating in any other clinical studies
- 16) Patients considered by the investigator/subinvestigator to be unsuitable for this study

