#### *Rationale for exclusion criteria*

- 1) To eliminate risk of enrolling patients with cardioembolic ischemic stroke
- 2) Anticoagulant agents are specified as prohibited concomitant medications
- 3) Prevents specified examinations
- 4) Evaluation will be strongly affected by these surgeries
- 5) Dual antiplatelet therapy is necessary for one year after the drug-eluting stent implantation
- 6) to 16) To secure the safety of study subjects based on the precautions for using cilostazol, aspirin, and clopidogrel

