## 11. Statistical Analysis

### 11.1. Rationale for target sample size

We assumed an annual recurrence rate of 4% in the monotherapy group based on data from the EVEREST study and the aspirin monotherapy group in the JASAP study. We also assumed a 30% decrease in relative recurrence risk (in other words, an annual relapse rate of 2.8%) in the DAPT group with cilostazol. The number of subjects required was calculated at 1,688 per group using the methods described by Lakatos et al in our main analytical method of the log-rank test (conditions were assumed relapse rates for each group, a 2.5 year enrollment period, a maximum 3.5 year observation period,  $\alpha=0.05$ , and a statistical power of 80%). This results in a total target sample size of 4,000 (2,000 per group), assuming an annual dropout rate of 5% during the study period.

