### **9.2.1 Stroke (ischemic stroke, intracerebral hemorrhage, subarachnoid hemorrhage)**

The first event involving ischemic stroke, intracerebral hemorrhage, or subarachnoid hemorrhage will be included in the analysis.

Subjects discontinued for reasons other than occurrence of an event included in the analysis and subjects who continue to study completion will be considered censored subjects. The censor date will be considered the observation completion date.

- 1) A between-groups comparison for the period from the observation start date to the date of ischemic stroke onset will be performed using the log-rank test, and the superiority of the combination therapy group versus the monotherapy group will be examined.
- 2) Survival coefficients for the period from the observation start date to the date of the event will be estimated for each treatment group using the Kaplan-Meier method and plotted.
- 3) The hazard ratio for the occurrence of an event in either of the 2 groups and its 95% confidence interval will be determined using the Cox proportional hazard model.

The same analysis described in section 9.2.1 will be performed for the events indicated in sections 9.2.2 to 9.2.6.

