### **9.2.5 Stroke (ischemic stroke, intracerebral hemorrhage, subarachnoid hemorrhage), myocardial infarction, or vascular death**

The first event involving ischemic stroke, intracerebral hemorrhage, subarachnoid hemorrhage,

myocardial infarction, or vascular death will be included in the analysis.

Subjects discontinued for reasons other than occurrence of an event included in the analysis and subjects who continue to study completion will be considered censored subjects. The censor date will be considered the observation completion date.

**9.2.6 All vascular events: stroke, myocardial infarction, and other vascular events [e.g., aortic dissection or rupture; pulmonary embolism; heart failure, angina pectoris, or occlusive arteriosclerosis requiring hospitalization; and revascularization (e.g., coronary artery, aorta, peripheral artery)]**

The first event involving stroke, myocardial infarction, or another vascular event [e.g., aortic dissection or rupture; pulmonary embolism; heart failure, angina pectoris, or occlusive arteriosclerosis requiring hospitalization; and revascularization (e.g., coronary artery, aorta, peripheral artery)] will be included in the analysis.

Subjects discontinued for reasons other than occurrence of an event included in the analysis and subjects who continue to study completion will be considered censored subjects. The censor date will be considered the observation completion date.

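### Hospitalised heart failure and angina get a time-to-event analysis only inside the all-vascular-events efficacy composite; the safety tables show them ungrouped and without time at risk

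*Supplement*

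**What the plan says.** Protocol v1.3, section 3.3, item 8 excludes "Patients with congestive heart failure or uncontrolled angina pectoris". One rationale covers exclusions 6 to 16: "To secure the safety of study subjects based on the precautions for using cilostazol, aspirin, and clopidogrel".

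As endpoints, the conditions appear only within all vascular events, a secondary efficacy endpoint (Protocol Summary and section 8.2), which includes "heart failure, angina pectoris, or occlusive arteriosclerosis requiring hospitalization". SAP 9.2.6 analyses "The first event involving stroke, myocardial infarction, or another vascular event" with the methods of 9.2.1: log-rank test, Kaplan-Meier and Cox model, where "the superiority of the combination therapy group versus the monotherapy group will be examined". No analysis by component is listed.

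The named safety endpoints (protocol section 9, SAP 2.3) are adverse events and adverse drug reactions, and severe or life-threatening hemorrhage. An adverse event that needs admission for treatment is serious (protocol 7.1.2), and section 6.3.3 points to the serious adverse event procedures. SAP 10.1 to 10.4 tabulate adverse events, adverse drug reactions and their serious subsets by system organ class and preferred term. Incidence is a percentage of ITT patients, compared by chi-square. The Independent Data Monitoring Committee (IDMC) sees serious adverse events and adverse drug events by treatment, in principle yearly (protocol 11.4).

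Under protocol 5.3, observation ends at any 6.3.3 event, at drug withdrawal beyond 4 weeks, or when study drug is discontinued.

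**The concern.** Bleeding, excluded under the same rationale (item 6), has a named safety endpoint, a grouped analysis in SAP 10.5 and its own line in the yearly IDMC review. Hospitalised heart failure and angina have none of these.

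Their one time-to-event analysis is a superiority comparison in which the planned stroke benefit pulls the other way. The safety tables do look at them separately from stroke, but scattered over terms or merged into a whole organ class, and without allowing for how long each arm was observed. At stake is how precisely, and with what bias, the trial can report an effect of added cilostazol on these admissions.

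**Working it through.** **Inputs from the documents.** Protocol 11.1: "We assumed an annual recurrence rate of 4% in the monotherapy group", 2.8% on the combination, and "a 2.5 year enrollment period, a maximum 3.5 year observation period". Protocol 10.1: 2,000 per group. Protocol 11.4.1: 8,000 person-years expected, taken here as 4,000 per arm.

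**The plan's own figure.** Schoenfeld events for a hazard ratio of 0.7, 80% power and two-sided 5%: 4 × (1.960 + 0.842)² / (ln 0.7)² = 247. With uniform accrual over 2.5 years and 3.5 years in total, the event probability is 1 − (e^(−λ) − e^(−3.5λ)) / (2.5λ). This gives 0.0857 at λ = 0.04 and 0.0609 at λ = 0.028, mean 0.0733. Then 247 / 0.0733 / 2 = 1,685 per group, against the stated 1,688. The rates are therefore read as intended.

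**Offset in the composite.** Strokes avoided = (4.0 − 2.8)/100 × 4,000 = 48. With equal person-time, the composite hazard ratio stays at or below 1 until the heart failure/angina excess passes 1.2 per 100 person-years. The break-even relative risk is (b + 1.2)/b for a single-therapy rate b: 7.0 at 0.2, 3.4 at 0.5 and 2.2 at 1.0 per 100 person-years.

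The documents do not give b, the relative risk or the rate of other vascular events; all three are assumed below.

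| b, % per year | Relative risk | Heart failure/angina events | Composite HR, no other events | Composite HR, other events 2% per year in both arms |
|---|---|---|---|---|
| 0.2 | 2 | 8 v 16 | 0.76 | 0.84 |
| 0.2 | 3 | 8 v 24 | 0.81 | 0.87 |
| 0.5 | 2 | 20 v 40 | 0.84 | 0.89 |
| 0.5 | 3 | 20 v 60 | 0.96 | 0.97 |
| 1.0 | 2 | 40 v 80 | 0.96 | 0.97 |
| 1.0 | 3 | 40 v 120 | 1.16 | 1.11 |

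An example with intervals, assuming 0.3 tripled to 0.9 and other events at 1.5 in both arms:
- Composite rates: 4.0 + 1.5 + 0.3 = 5.8 v 2.8 + 1.5 + 0.9 = 5.2, so 232 v 208 events. HR 0.90; SE of log HR = √(1/232 + 1/208) = 0.095; 95% CI 0.74 to 1.08.
- Heart failure/angina alone: 12 v 36. HR 3.0; SE = √(1/12 + 1/36) = 0.333; 95% CI 1.6 to 5.8.

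**What the planned safety test would show.** Chi-square on that example, 2,000 per arm and one event per patient: 12 v 36 gives p = 0.0005. Split evenly over two terms (6 v 18) p = 0.014, three (4 v 12) p = 0.045, four (3 v 9) p = 0.083.

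Power for a doubling, with 2,000 per arm followed for 2 years:

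| b, % per year | Chi-square, one term with half the events | Chi-square, all grouped | Grouped time to event |
|---|---|---|---|
| 0.2 | 21% | 37% | 40% |
| 0.5 | 44% | 73% | 77% |
| 1.0 | 72% | 95% | 97% |

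Most of the gain comes from grouping.

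**Time at risk.** Take b = 0.5% per year, truly doubled. Assume mean follow-up of 2.0 years on single therapy and 1.7 on the combination. Events: 2,000 × 0.005 × 2.0 = 20 v 2,000 × 0.010 × 1.7 = 34. The crude ratio is 34/20 = 1.7. The rate ratio is (34/3,400) / (20/4,000) = 2.0.

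**The case against.** The strongest reply is that the safety objective is answered by SAP section 10, not by the composite. These admissions are adverse events and serious adverse events, and adverse drug reactions where causality cannot be denied. All are compared between arms and tabulated by treatment for the IDMC. Protocol 24.1 asks for the diagnosis in place of symptoms, which limits scatter over terms, and the organ-class line does pool. The planned chi-square detects the 12 v 36 example even when split over three terms. All of this stands.

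A reader might therefore infer too much in three ways:
- **That an excess is hidden, or that these events are not a safety endpoint.** The adverse event tables contradict both.
- **That the safety objective would be answered wrongly.** That would require ignoring section 10. In the worked example the composite itself (0.74 to 1.08) does not show superiority.
- **That the protocol forecasts new heart failure on cilostazol.** The rationale is one sentence for eleven exclusions and three drugs. Excluding an existing condition is not a prediction of incident cases.

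The reply does not supply a grouped estimate. The organ-class total mixes these conditions with others, a single term holds only part of the events, and neither level uses person-time.

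**Conclusion.** The point holds as a gap in measurement. The only time-to-event analysis containing hospitalised heart failure and angina is an efficacy composite in which a planned stroke benefit of about 48 events can offset an excess. The separate safety look exists but is less sensitive: 44% against 77% power for a doubling at 0.5% per year, if one term holds half the events. It can also understate an excess, with a true ratio of 2.0 reading as 1.7 if mean follow-up on the combination is 1.7 rather than 2.0 years.

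The direction of that bias is not fixed. More drug discontinuation on the combination would shorten its follow-up, whereas fewer strokes would lengthen it. The offset is conditional too: it depends on the assumed heart failure/angina rate and on the planned stroke effect appearing, and a tripling at 1.0% per year would take the composite to 1.11 to 1.16.

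**What to change.** In SAP section 10, add one grouped safety comparison from the dated 6.3.3 records: by arm, the count and person-time rate, with hazard ratio and 95% CI, for hospitalised heart failure, for hospitalised angina, and for either. In SAP 9.2.6, report component counts by arm beside the composite. Include the grouped count in the yearly by-treatment table for the IDMC.

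No new data are needed: protocol 6.3.3 records date and details, and SAP 6.2.5 already derives days to onset. The cost is one extra table and some SAP wording, and the intervals will be wide (1.6 to 5.8 for 12 v 36 events). The hazard ratio allows for unequal follow-up. It does not recover events after observation has stopped, nor correct for stopping related to risk, and the table should say so.

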## Study Design

[figure not shown]

## Observation schedule

| Time point
Evaluation items               | (Date of onset) | Enroll-ment | Start of obser-vation | Month 1   | Month 3 | Month 6 | Month 12 | Every 6 months there-after | End of obser-vation (*) |
|----------------------------------------------|-----------------|-------------|-----------------------|-----------|---------|---------|----------|----------------------------|-------------------------|
| Informed consent                             | ← ○             |             |                       |           |         |         |          |                            |                         |
| Enrollment                                   |                 | ○           |                       |           |         |         |          |                            |                         |
| Observation status                           |                 |             |                       | ○         | ○       | ○       | ○        | ○                          | ○                       |
| Patient characteristics                      | ← ○             |             |                       |           |         |         |          |                            |                         |
| Degree of independence in daily living (mRS) |                 |             | ○                     | ○         | ○       | ○       | ○        | ○                          | ○                       |
| Study drug administration/ compliance        |                 |             | ○                     | ○         | ○       | ○       | ○        | ○                          | ○                       |
| Drugs other than study drug                  |                 |             | ○                     | ○         | ○       | ○       | ○        | ○                          | ○                       |
| Blood pressure                               |                 |             | ○                     | ○         | ○       | ○       | ○        | ○                          | ○                       |
| Head MRI                                     | ← ○             |             |                       |           |         |         |          |                            |                         |
| Head MRI (T2* WI)                            | ← △ →           |             |                       |           |         |         |          |                            |                         |
| Head MRA                                     | ← △ →           |             |                       |           |         |         |          |                            |                         |
| Carotid artery imaging                       | ← △ →           |             |                       |           |         |         |          |                            |                         |
| Laboratory test (blood)                      | ← ○ →           |             |                       | ← ..... → |         |         |          |                            |                         |
| Laboratory test (urine)                      | ← ○ →           |             |                       | ← ..... → |         |         |          |                            |                         |
| Chest x-ray                                  | ← ○ →           |             |                       | ← ..... → |         |         |          |                            |                         |
| ECG                                          | ← ○ →           |             |                       | ← ..... → |         |         |          |                            |                         |
| Adverse events                               |                 |             | ← ..... →             |           |         |         |          |                            |                         |

○ Required item △ Optional item ← ..... → As required

\* Observation is complete when a subject meets criteria for discontinuation/completion, or when 1 year has elapsed from initiation of observation for last subject enrolled.

## 1. Study Objectives

To evaluate the efficacy and safety of dual antiplatelet therapy (DAPT) including cilostazol (Pletaal OD Tablet®) in comparison with single antiplatelet therapy (SAPT) excluding cilostazol for secondary prevention of ischemic stroke in high-risk patients.

## 2. Background and Rationale

### 2.1. Present state of dual antiplatelet therapy in preventing ischemic stroke recurrence

Currently, treatment with antiplatelet drugs is strongly recommended for preventing recurrence of noncardioembolic ischemic stroke, along with improvement of the lifestyle and management of risk factors. However, prophylactic efficacy of aspirin for vascular events, for which there is significant evidence, shows a relative risk reduction rate (RRR) of only 20 to 30%. Existing antiplatelet monotherapy does not have sufficient prophylactic efficacy for stroke recurrence, especially in patients with overlapping risk factors such as intracranial artery stenosis, carotid stenosis, and diabetes mellitus/hypertension. Therefore, stronger antiplatelet drugs development or dual antiplatelet therapies with different mechanism of action are being examined to enhance prophylactic efficacy for vascular events in patients at high risk for ischemic stroke (IS) or transient ischemic attack (TIA).

With regard to dual antiplatelet therapy, efficacy of combined aspirin and extended-release dipyridamole in IS/TIA patients was confirmed in the ESPS 2 (European Stroke Prevention Study) and ESPRIT (European/Australasian Stroke Prevention in Reversible Ischaemia Trial) studies. However, in Japan, the JASAP study [Japanese Aggrenox (Extended-Release Dipyridamole plus Aspirin) Stroke Prevention versus Aspirin Programme] failed to demonstrate the efficacy of this combination, and dipyridamole has not been approved to prevent recurrence of ischemic stroke.

With regard to the combined effect of aspirin and clopidogrel in IS/TIA patients, results of CARESS (Clopidogrel and Aspirin for Reduction of Emboli in Symptomatic Carotid Stenosis), FASTER (Fast Assessment of Stroke and Transient ischaemic attack to prevent Early Recurrence), CLAIR (Clopidogrel plus aspirin versus aspirin alone for reducing embolisation in patients with acute symptomatic cerebral or carotid artery stenosis), etc., demonstrated the efficacy of combined treatment in patients with IS/TIA at relatively early stage of onset. Efficacy of a short-term combination therapy of aspirin and clopidogrel was also demonstrated in the recent CHANE study (Clopidogrel in High-risk patients with Acute Non-disabling Cerebrovascular Events). However, long-term combined use of aspirin and clopidogrel is not recommended as it increases serious bleeding complications, even though there is no change or even a slight decrease observed in vascular events.

